### 8.2.2 Immunogenicity Assays

Immunogenicity testing will be performed by qualified laboratories which are reference on influenza, namely Instituto Adolfo Lutz and Fundação Oswaldo Cruz using qualified assays already in established protocols. For these assays, serum specimen collection will occur on visits V1 (prior to injection of study products), V2 (prior to injection of study products), S2 (HI only) and I.

Serum Antibody to Influenza Virus Detected by Hemaggluttinin Inhibition Assay (HI)

The HI is the most frequently used serologic test for determining immunologic response to influenza vaccination. Serum specimens will be tested for the presence and titer of HI antibodies to the H7N9 influenza strain represented in the vaccine at a qualified laboratory according to established procedures. The HI assay will be conducted on serum samples from all the participants of the study in one or more Brazilian laboratories, and may also be performed in a laboratory abroad in order to confirm the results found in the laboratory (s) in Brazil, if deemed necessary by the parties involved in conducting the study.

Serum Antibody to Influenza Virus Detected by Microneutralization Assay (MNT)

The microneutralization assay is an alternative test for determining immunologic response to influenza vaccination and will be conducted in serum samples from participants as asecondary immunogenicity endpoint by one or more qualified laboratory (which may be located outside Brazil).

Regarding the sending of samples abroad, all aspects of the Brazilian laws will be complied with, according to resolution CNS no. 441 of 2011 in item 14.

### 8.2.3 Preparation, Processing and Specimens

Blood Specimens

Blood will be collected according to universal precautions for testing in multiple assays. Serum for the following: blood chemistry, HBV, HCV and HIV serology, HI antibody serology. Whole blood is collected for WBC, Hgb, Hct, and platelets.

|  | **Volume of blood** | **Day of Screening** | **V1**  **(pre-vac)** | **S1** | **V2**  **(pre-vac)** | **S2** | **I** |
| --- | --- | --- | --- | --- | --- | --- | --- |
| Whole blood for Hematology | 4 mL | ✓ |  | ✓ | ✓ | ✓ |  |
| Serum for serology for HBV, HCV and HIV infection | 8,5 mL | ✓ |  |  |  |  |  |
| Serum for biochemical parameters | 5 mL | ✓ |  | ✓ | ✓ | ✓ |  |
| Serum for anti-influenza serologic assays | 30,5 mL |  | ✓ |  | ✓ | ✓ | ✓ |

(The total volume of blood planned to be collected from each participant during the course of the study will be less than 170 milliliters.)

# Assessment of Safety and Adverse Events

## 9.1 Definition and Categorization of AEs

The primary objective of this study is to evalute the safety profile and immunogenicity of the vaccine candidates. An AE (adverse event) is defined as any untoward medical occurrence in a participant administered an study product, which may or may not bear a causal relationship with this study injection. An AE can therefore be any unfavorable and unintended sign (including an abnormal laboratory finding), symptom, or disease temporally associated with the use of a medicinal product, whether or not considered related to the medicinal product. A subset of AEs, those commonly observed after influenza vaccine administration are described in the Participant Diary and will be specifically requested for 7 days post each study injection. Those AEs are termed “solicited” and will be evaluated for potential relationship with study product. Out-of-range laboratory abnormalities observed after study injections will be graded according to the grading table (see Table 5) and their clinical significance and potential relationship to study product assessed. Only those laboratory abnormalities greater than Grade 1 will be recorded as AEs.

All AEs should be graded using the Tables for Grading AEs (Tables 4, 5 and 6). These tables contain list of specific clinical and laboratory safety measurements of interest to the study. All clinical safety evaluations must be made by a qualified physician.

Any clinical sign or symptom or laboratory finding at any time-point might be categorized as an SAE if it meets the criteria established.

All adverse events will be MedDRA coded.

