## 8.2 Laboratory Evaluations

### 8.2.1 Clinical Laboratory Evaluations

All biochemical and hematological testing will be performed at a laboratory associated with the study sites in Brazil. The laboratories should follow GLP standards.

Laboratories will follow written procedures for conducting all laboratory assays.

Normal value ranges will be considered according to each clinical laboratory conducting tests. A Toxicity Table for Grading AEs, including out-of-range laboratory values, is included in section 9.3.

A laboratory result that is out-of-range but no greater than Grade 1 does not qualify as an AE and does not require determination of clinical significance or relatedness to the study products. A result will be checked as not clinically significant “NCS” on the laboratory result CRF if it is outside the lab range but lower than Grade 2.

Serology for Viral Infections (Screening only)

Blood specimens will be evaluated for the following using tests routinely used in the laboratories:

- Hepatitis B virus surface antigen (HBsAg)
- HCV antibody using anti-HCV test
- HIV serology testing

Specimen collection will occur on Day of screening. Pre and post-test counseling will be offered to participants according to protocols of the Brazilian Ministry of Health. Likewise, patients who test positive for any of the serological tests will be referred for appropriate prevention, treatment and care services. There will be coordination with laboratory services to support quality assurance and delivery of correct results. Determinant results of a participant’s testing must be obtained from the laboratory and evaluated prior to administration of any study product.

Pregnancy Test

In order to confirm pregnancy status of females, a qualitative human chorionic gonadotropin (hCG) test will be done on a urine sample collected on Day of Screening and before each study injection. No injection of study product may be given to a woman without a pregnancy test being done and to any woman with a positive pregnancy test.

Blood Chemistry and Hematology

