Specimen collection will occur on visits T, S1, V2 e S2. Results of testing for the participant will be reviewed by a study physician. Considering the tests of visits S1 and S2, out-of-range results Grade 2 and above will be assessed for clinical significance and relatedness to study injection and repeated. Any results that are Grade 2 or above and clinically significant should be followed until normal or stabilized prior to termination of participant participation in the study. “Clinically significant” means the result warrants further medical investigation or treatment because it may have impact on a person’s health status. If the clinician is unsure of clinical significance, the specimen should be re-drawn and the test re-run.

Blood Chemistry

- Creatinine
- Alanine aminotransferase (ALT, also called SGPT)
- Aspartate aminotransferase (AST, also called SGOT)
- Total bilirubin

Hematology

- Number of WBC and differentials
- Hemoglobin (Hgb)
- Hematocrit (Hct)
- Platelet count

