**Table 5 Classification of the severity of the laboratory adverse events.**

| **Adverse event** | **Grade 1** | **Grade 2** | **Grade 3** | **Grade 4** |
| --- | --- | --- | --- | --- |
| Hemoglobin decrease compared to baseline - gm/dL | 0.1 – 1.5 | 1.6 – 2.0 | 2.1 – 5.0 | >5.0 |
| Hemoglobin (women) - gm/dL | 11.0 – 12.0* | 9.5 – 10.9 | 8.0 – 9.4 | <8.0 |
| Hemoglobin (men) - gm/dL | 12.5 – 13.5* | 10.5 – 12.4 | 8.5 – 10.4 | <8.5 |
| Leukocytosis – cell/mm3 | 10,800^†^– 15,000 | 15,001 – 20,000 | 20,001 – 25,000 | >25,000 |
| Leukopenia – cell/mm3 | 2,500 – 3,500* | 1,500 – 2,499 | 1,000 – 1,499 | <1,000 |
| Lymphopenia – cell/mm3 | 750 – 1,000* | 500 – 749 | 250 – 499 | <250 |
| Neutropenia – cell/mm3 | 1,000 – 1,499* | 500 – 999 | 300-499 | <300 |
| Platelets Decreased – cell/mm3 | 125,000 – 140,000* | 100,000 – 124,000 | 25,000 – 99,000 | <25,000 |
| Creatinine – mg/dL | 1.5^†^ – 1.7 | 1.8 – 2.0 | 2.1 – 2.5 | >2.5 or requires dialysis |
| ALT/AST – increase by factor | 1.1 – 2.5 x ULN | 2.6 – 5.0 x ULN | 5.1 – 10 x ULN | >10 x ULN |
| Bilirubin – when accompanied by any increase in ALT/AST – increase by factor | 1.1 – 1.25 x ULN | 1.26 – 1.5 x ULN | 1.51 – 1.75 x ULN | >1.75 x ULN |
| Bilirubin – when ALT/AST are normal – increase by factor | 1.1 – 1.5 x ULN | 1.6 – 2.0 x ULN | 2.0 – 3.0 x ULN | >3.0 x ULN |

ILN: inferior limit of the normal range.

ULN: upper limit of the normal range.

* If the ILN is less than the upper limit of Grade 1, the ILN will be used as an upper limit to Grade 1.

^†^ If the ULN is greater than the lower limit to Grade 1, the ULN will be used as a lower limit to Grade 1.

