### 9.3.8 Procedures for Out-of-range Laboratory Test Values

Out-of-range laboratory values and AEs. To the extent possible, all reference ranges for clinical laboratory test results will be pre-specified. The site staff will follow the Toxicity Table (Table 5). Laboratory values that are out-of-range will not be considered an AE unless they qualify as a Grade 2 or above on the Toxicity Table. The reference ranges for the laboratory will be taken in to consideration when determining out of range results.

Out-of-range test values may be considered an SAE if two circumstances are met:

1. the value rises to the level of Potentially Life-threatening (Grade 4), and
2. the event is determined by the Principal Investigator to pose an immediate risk of death.

A Grade 4 laboratory result does not, in and of itself, constitute an SAE. Grade 4 places a laboratory value as a potentially life-threatening event, but a Grade 4 laboratory result should not be reported as an SAE unless the PI has determined that it does, in fact, pose an immediate risk of death.

Assessing relatedness and clinical significance of out-of-range laboratory values: All laboratory results should be reviewedAny laboratory finding Grade 2 and above is regarded as an AE. The investigator will assess relatedness and clinical significance for these findings.

Clinical judgment always should be used to determine whether a laboratory result requires additional follow up. However, the investigator should redraw any Grade 2 or above laboratory result that is deemed clinically significant at an unscheduled visit to check if the result has normalized.

Any Grade 2 or above laboratory value that is clinically significant and has not returned to normal or stabilized by day V2+194 should be marked by the investigators as “continuing” or “unresolved.” The investigator should assure that the participant is referred for appropriate medical follow-up, if indicated.

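### The only stated route for a laboratory result to become an AE is Grade 2 or above on Table 5, but Table 5 has no row for some results the trial measures, such as raised platelets

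*Protocol*

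**What the plan says.** Section 9.1 first defines an AE broadly enough to include an abnormal laboratory finding. It says that out-of-range results after injection "will be graded according to the grading table (see Table 5"), with their clinical significance and possible relationship to study product also assessed. It then narrows what is recorded: "Only those laboratory abnormalities greater than Grade 1 will be recorded as AEs".

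Section 9.3.8 names the same table ("The site staff will follow the Toxicity Table (Table 5")) and states the rule in the negative: "Laboratory values that are out-of-range will not be considered an AE unless they qualify as a Grade 2 or above on the Toxicity Table".

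Section 8.2.1 lists the haematology panel as "Number of WBC and differentials", haemoglobin, haematocrit and platelet count. The chemistry panel is creatinine, ALT, AST and total bilirubin. The same section has a result marked as not clinically significant (NCS) "on the laboratory result CRF if it is outside the lab range but lower than Grade 2".

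Section 11.5 includes abnormal laboratory findings from Days 7 and 35 among the adverse events to be analysed and gives no grade limit.

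**The concern.** A threshold expressed as a grade works only where a grade exists. For a result with no row in Table 5 the Grade 2 condition cannot be met, whatever the value. Neither 9.1 nor 9.3.8 lets clinical significance serve as another way in. In 9.3.8 it is assessed for findings already at Grade 2 or above.

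This is the first human use of these antigen and adjuvant combinations (section 1.6.1), and safety is a primary objective (2.2.1). Safety blood is drawn largely to find changes that cause no symptoms. A site following 9.3.8 literally would not record a marked, symptomless rise in platelets as an AE, while a site following the definition in 9.1 would. The analysis plan cannot recover events that sites were told not to record.

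**Working it through.** The point rests on no sample-size or power figure, so the check compares passages.

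**Step 1. What is measured, against Table 5.** Table 5 has 12 rows: three for haemoglobin, one each for leukocytosis, leukopenia, lymphopenia, neutropenia, decreased platelets, creatinine and ALT/AST, and two for bilirubin (3 + 7 + 2 = 12).

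| Result (8.2.1) | Low-side row | High-side row |
|---|---|---|
| Haemoglobin | Yes | None |
| Haematocrit | None | None |
| Total WBC | Yes | Yes |
| Neutrophils | Yes | None |
| Lymphocytes | Yes | None |
| Other differential cell types | None | None |
| Platelets | Yes ("Platelets Decreased – cell/mm3") | None |
| Creatinine, ALT, AST, total bilirubin | None (not relied on here) | Yes |

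The other differential cell types would be eosinophils, monocytes and basophils if the differential is a standard one. The protocol does not name them.

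**Step 2. Which panel applies after injection.** The visit descriptions for S1 (7.2.3) and S2 (7.2.7) list only WBC, haemoglobin and platelets for haematology. Section 8.2.1 lists the fuller panel for T, S1, V2 and S2, and 8.2.3 also includes haematocrit. The lymphopenia and neutropenia rows in Table 5 suggest that a differential is intended.
- Short list: raised platelets and raised haemoglobin have no row.
- Fuller list: haematocrit, raised neutrophils, raised lymphocytes and the other cell types are added.

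The gap exists on either list.

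**Step 3. Is there another route?**
- Section 9.3.5 says what to do when no grading scale is provided, but it concerns solicited reactions.
- Table 6 grades unsolicited clinical events.
- The laboratory SAE route in 9.3.8 requires Grade 4 plus an immediate risk of death, so it also needs a grade.
- The laboratory halting criteria in 9.6 count Grade 3 or Grade 4 abnormalities, and laboratory SAEs are excluded from the SAE halting event and referred back to 9.3.8.

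None of these gives a recording route for an isolated laboratory abnormality without a grade.

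**Step 4. Consistency.** The AE definition in 9.1 admits an abnormal laboratory finding, and 11.5 counts such findings with no grade stated. The recording rule in 9.1 and 9.3.8 excludes any result that has no Table 5 grade. The passages cannot all be followed for such a result.

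**The case against.** The strongest reply is that Table 5 is a deliberate selection: 9.1 presents the grading tables as lists of measurements of particular interest, and grading chosen parameters in chosen directions is a legitimate design decision. That stands as a defence of the choice of rows. It does not explain what a site should do with a clinically significant result outside them.

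Several further points also stand, and they limit the finding:

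- Some changes would show through a graded result. A fall in haematocrit would usually appear through haemoglobin, and a large rise in one cell type may push total WBC into leukocytosis. The second is not reliable, because leukocytosis reaches Grade 2 only at 15,001 cells/mm3. Raised platelets have no such proxy.
- An illness that follows from the abnormality can be recorded as a clinical AE under Table 6, and the important-medical-event criterion for an SAE in 9.3.7 remains available.
- A reader might infer that these results escape assessment of relatedness. The text does not support that, because 9.1 calls for the significance and relationship of out-of-range results to be assessed. Section 9.3.8 adds that all laboratory results should be reviewed and that clinical judgment governs follow-up.
- A reader might infer that an ungraded result must be marked NCS. Section 8.2.1 says this of results below Grade 2 and is silent on results with no grade, so that is an inference only.
- A reader might infer that such findings can never reach the safety analysis. Section 11.5 points the other way, which makes this a contradiction to resolve and not an established exclusion.

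**Conclusion.** The fault is real but limited. Under the recording rule in 9.1 and 9.3.8, a clinically significant isolated abnormality in a result with no Table 5 row cannot be recorded as a laboratory AE and cannot count towards the grade-based halting criteria. This holds for raised platelets and raised haemoglobin on any reading of the panel. For haematocrit, raised neutrophils, raised lymphocytes and the other differential cell types it holds if the 8.2.1 panel is the one drawn.

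The number of results affected cannot be estimated from the document. A reader might apply an assumed rate to the S1 and S2 samples (432 × 2 = 864), but the protocol gives no such rate. A rate of out-of-range values would also count trivial results that would not be AEs under any sensible rule.

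A reader might also infer that the comparison between arms is biased. Nothing in the document shows this: the rule is the same in every arm and is applied blind. What is shown is that a symptomless signal in one of these results could go unrecorded, and that sites could handle the same result differently.

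**What to change.** Reconcile 9.1, 9.3.8, 8.2.1 and 11.5:

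1. Limit the Grade 2 threshold in 9.1 and 9.3.8, and the NCS sentence in 8.2.1, to results that have a row in Table 5.
2. Add to 9.1 and 9.3.8: *An out-of-range post-injection result in a parameter or direction without a row in Table 5 is assessed by the study physician. If judged clinically significant, it is recorded as an AE regardless of grade, and its relationship to study product is assessed.*
3. Make 11.5 refer to the same rule, so that what is analysed matches what is recorded.
4. Reconcile the analyte lists in 7.2.3, 7.2.7 and 8.2.1.

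The words *regardless of grade* are needed. Sending these results to Table 6 alone would not work: a symptomless finding does not interfere with daily activities, so it would be Grade 1 and the sentence in 9.1 would still exclude it.

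This change does not bring such results into the halting counts, which need a grade. Whether to add Table 5 rows or halting cut-offs, and at what values, is for the sponsor.

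The cost is a few sentences and a matching note in the CRF instructions. No new test is needed, since the study physician already reviews the results. The downside is a few more AEs to record.

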## 9.2 Specification of Safety Parameters

The safety profile will be evaluated by the proportion of participants experiencing AEs, related or not related, of the following four categories:

- Adverse events occurring over the immediate 30-minute post each study injection.
- Number and percentage of participants with solicited local AE (erythema, swelling/induration, pain/tenderness, ecchymosis, pruritis) over the 7-day period post each study injection.
- Number and percentage of participants with solicited systemic AEs (fever, fatigue/malaise, myalgia, arthralgia, chills, nausea/vomiting, and headache) over the 7-day period post each study injection.
- Number and percentage of participants with unsolicited adverse events for 28 + 7 days post each study injection.
- All serious adverse events (SAEs) occurring over the entire study period.

## 9.3 Methods and Timing for Assessing and Recording Safety Parameters

### 9.3.1 Adverse Events

The occurrence of an AE might come to the attention of study personnel during study visits and interviews of a study participant presenting for medical care. Information to be collected on AEs includes event description, time of onset, clinician’s assessment of severity, relationship to study product, and time of resolution/stabilization of the event. AE assessment should be made only by those with the training and authority to make a diagnosis.

Any medical condition that was present at the time that the participant was enrolled should not be reported as an AE, but should be reported as a pre-existing condition on the Medical History Form. However, if this condition occurs with greater frequency or severity during the study, it should be recorded as an AE.

AEs, including laboratory abnormalities that are Grade 2 and above, should always be assessed for severity and relationship to study products.

This study will collect and record solicited and unsolicited local and systemic AEs (described in further detail in section below). For clarity, solicited AEs refer specifically to those asked about during the 7-day post study injection period. Unsolicited events are those not specifically solicited, but may be reported by the participant at any time or observed by study staff while the participant is at a clinic for a study visit. Unsolicited events are recorded up through 28 + 7 days post each study injection, except for SAEs, which are recorded throughout the entire study period as required (V2+194 days). If a new solicited event is reported by the participant outside of the 7-day post-vaccination window, this event will be recorded as an “unsolicited AE” because it will be outside of the 7-day window for collection of solicited reactogenicity.

